## **Methods**

**Study Overview:** This study is a two-site, parallel group, RCT comparing a technology assisted SCCI (TĀCcare) to technology-assisted health education control in improving key patient-centered outcomes in 150 HD patients. After signing informed consent, completing baseline assessments and meeting eligibility criteria, enrolled patients will be randomized 1:1 to TĀCcare or technology-delivered health education and will undergo a 12-week intervention. The study participants will be recruited using an approach to limit drop-out while enhancing generalizability and the main analysis is intention-to-treat. The main patient-centered outcomes (**Aim 1**) are: 1) a clinically meaningful change (effect size 0.6) in depression, pain or fatigue (*primary outcome*); 2) a change in HRQOL and ecological momentarily assessed composite symptom score of fatigue, sleepiness and mood (*secondary outcomes*) after the 12-week intervention. We will also determine the effect of TĀCcare on adherence to medications, diet and HD treatments (*secondary outcomes*) (**Aim 2**) and we will explore changes in inflammatory biomarker levels (**Aim 3**) after the 12-week intervention. Since the effect of pharmacotherapy may be delayed, we will measure these outcomes at 6 months and again at 12 months to assess the maintenance of the benefits of our intervention.

**Setting and Participants:** A total of 150 adult chronic HD patients will be recruited from the two clinical sites at the University of Pittsburgh and the University of New Mexico which collectively have 20 free-standing dialysis clinics that vary in geographic areas, size and population served. These clinics were selected to ensure a diverse HD population with adequate representation of females and minority groups including African Americans, American Indians and Hispanic/Latinos.

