**Duration of Intervention and Follow-Up:** Each participant will be treated in the assigned group for 12 weeks, death, or loss to follow-up (withdrawal from study, transfer of dialysis clinic, change to peritoneal dialysis or transplantation). The length of intervention was selected based upon national guidelines recommending 8-12 weeks of weekly CBT or initial pharmacological treatment of depression as well as our prior results showing successful efficacy of a similar 12-week intervention in cancer patients. If there is any acute change in patient's medical condition/hospitalization during the intervention period, patients will be re-evaluated for their ability and interest to continue participation once medically stable. If needed, the intervention period will be prolonged to complete a total of 12 sessions so that patients have an opportunity to receive adequate treatment and derive cumulative benefit. Outcomes will be assessed again at 6 months to evaluate the intermediate effect of intervention, as it is possible that some patients may not receive intensified interventions (including pharmacotherapy) until late in the window for intervention and will likely not have an immediate effect on the outcomes. A number of studies and meta-analyses evaluating long term effect of 8-12 weeks of CBT or collaborative care on depression, fatigue, or pain show sustained benefit at 12 months. Whether such sustained effects are seen in this patient population, remains to be evaluated. Thus, we are evaluating the effects of TACcare at 6 months and 12 months to assess the long-term effect of our intervention.

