Thus, our sample size provides 88% power to detect an effect size of 0.6 controlling for 5% FDR for 3 endpoints assuming a true difference exists in 1 out of 3 endpoints. If differences exist on 2 of 3 endpoints, we will have 89% power to detect an effect size of 0.5. The detectable effect size is consistent with what we observed in our study of SCCI in cancer patients (effect size was 0.7 for depression, 0.6 for pain and 0.3 for fatigue, respectively).

In May 2020, the sample size was increased to 160 participants per DSMB recommendations given a higher observed attrition rate (14%).

**General Statistical Approach:** Distributions of baseline characteristics will be compared between the groups to assess effectiveness of randomization, and statistical differences will be accounted for as covariate in secondary adjusted analyses. All primary analyses will be adjusted for site, age, and comorbidity (design variables) as well as sex and unadjusted analyses will also be reported per CONSORT recommendations. The stratification variables are potentially prognostic of the outcomes, which likely will make the adjusted analyses more efficient than unadjusted. The primary analyses will use the 'intent-to-treat' approach in which subjects are analyzed in their assigned group, regardless of treatment adherence, withdrawal or deviation from protocol. General linear mixed models (GLMM) will be used for inferential analyses of primary and secondary outcomes. Unless otherwise specified, all tests will be conducted using two sided 5% level of significance. We will report our findings according to the CONSORT guidelines.

**Preliminary Analyses** will focus on data checks for completeness and accuracy and address any issues with data quality. The preliminary exploration of the data will be used to: 1) examine univariate and bivariate distributions; 2) identify any imbalances between treatment groups on baseline characteristics; 3) investigate the magnitude of the associations between the dependent variables and the potential covariates; 4) verify the statistical assumptions of the planned primary analyses. If assumptions are violated, then alternative procedures such as data transformations or more robust statistical methods will be considered.

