**Secondary Outcomes Analyses:** Our secondary patient-reported outcomes are changes in HRQOL (SF-12 mental and physical component score) in TACCare versus control arm after a 12-week intervention. EMA-measured composite symptom severity score will be evaluated at baseline and post-intervention (12 weeks). Adherence outcomes include adherence to medications, diet and dialysis treatments (all continuous variables) measured at 12-weeks, and at 6-and 12-months follow-up. Biomarkers of inflammation include hs-CRP, IL-6, IL-10, and TNF- $\alpha$  measured at baseline, 12-week, and 6-months follow-up. GLMM will also be used to analyze these outcomes. Benjamini-Hochberg correction will be applied to the biomarker analyses. We will also assess the bi-directional association and calculate correlations between the biomarkers and symptoms. Moreover, we will examine how adjusting for the biomarkers influences the TACCare effect on the symptoms, and how adjusting for the symptoms influences the effect on the biomarkers.

**Subgroup Analyses:** The response to treatment interventions may differ among certain patient subgroups. Thus, to explore heterogeneity of intervention effects, we will examine pre-specified subgroups including age – age $\leq$ 65, age $>$ 65; sex – male, female; race – white, black, others; Charlson comorbidity index – less than 4, 4 or more; and dialysis vintage  $\leq$  1 year, vintage  $>$  1 year. Each variable, its two- and three-way interaction with the treatment group and with time were added to the model, and linear contrasts were used to test for heterogeneity of treatment effects. In addition, we will estimate the treatment effects among those who had elevated symptoms at baseline (FACIT-F $\leq$ 44, BDI $\geq$ 16, BPI $\geq$ 5).

**Sensitivity analyses:** We will perform additional analyses to assess the robustness and potentially refine our conclusions. This would include assessing intervention as-treated rather than intention-to-treat, nonlinearity of time in the EMA fatigue model, impact of outliers or influential points and impact of missing data.

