**Intercurrent events (ICE):** To maintain a consistent approach, we have selected a hypothetical strategy as our primary approach to handle all ICEs (death, Kidney transplant, switching to home dialysis, patient relocated, withdrawal, treatment dropout/discontinuation, treatment paused due to COVID) to estimate what would have been the outcome at the follow-up time points had the ICE did not occur. Thus, only data that were observed prior to the occurrence of the ICE will be used in fitting mix models for the primary analyses. We opted to keep using mixed models as the primary analytic approach to execute the hypothetical strategy to take advantage of the longitudinal data collection and hence makes more efficient use of available data. This approach assumes post-ICE outcomes can be predicted using observed pre-ICE outcomes and other measured characteristics.

**Missing Data:** The extent, reasons, randomness of missing data will be examined to identify possible covert missing data mechanisms. Baseline characteristics and intermediate outcomes among those who do or do not complete the study will be compared. The primary analytical approaches (GLMM) can handle data that are ignorably missing (i.e., either missing completely at random or missing at random). However, strategies to handle missing data (single/multiple imputation, selection models, pattern-mixture models, etc.) and sensitivity analyses to encompass different scenarios of assumptions will be considered as appropriate. For measures that were missing due to non-response at the item-level, multiple imputation by chained equations will be used to impute the response at the item level. The median value across 5 imputed datasets will be used in the calculation of overall score.

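### The primary analysis is called intention-to-treat, yet its hypothetical strategy drops all data after any intercurrent event; the two target different effects unless benefit fully persists

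*Protocol*

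**What the plan says.** Two statements describe the primary analysis as intention-to-treat. The Study Overview (Protocol, Methods) says "the main analysis is intention-to-treat". The General Statistical Approach (Original Statistical Analysis Plan) says of the primary analyses that "subjects are analyzed in their assigned group, regardless of treatment adherence, withdrawal or deviation from protocol".

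The paragraph on intercurrent events in the same plan says otherwise: "we have selected a hypothetical strategy as our primary approach to handle all ICEs". Besides death and kidney transplant, its list of events names "switching to home dialysis, patient relocated, withdrawal, treatment dropout/discontinuation, treatment paused due to COVID". On the data used it says that "only data that were observed prior to the occurrence of the ICE will be used in fitting mix models for the primary analyses", and it states its premise: "This approach assumes post-ICE outcomes can be predicted using observed pre-ICE outcomes and other measured characteristics".

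Three other places bear on this:
- The Sensitivity analyses paragraph includes "assessing intervention as-treated rather than intention-to-treat", which takes for granted that the primary analysis is intention-to-treat.
- Duration of Intervention and Follow-Up ends a patient's time in the assigned group at 12 weeks, death, or "loss to follow-up (withdrawal from study, transfer of dialysis clinic, change to peritoneal dialysis or transplantation".
- The Patient-Reported Outcomes paragraph has the questionnaires given by central telephone interview, with the patient at home on a non-dialysis day, at baseline, 12 weeks, 6 months and 12 months.

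**The concern.** The General Statistical Approach says that adherence and withdrawal do not affect how a subject is analysed. The intercurrent-event paragraph makes those same things decide whether a subject's later scores are used. Both are current text about the primary analysis, under one plan heading, so an analyst cannot follow both.

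What is at stake is the meaning of the main result. Aim 1 concerns effectiveness. An intention-to-treat reading answers what happens when TACcare is offered, including to people who stop. The hypothetical reading answers what would have happened had nobody stopped, paused, moved or died. A report that calls the second by the name of the first would mislead its readers, and no analysis named in the protocol keeps the post-event scores so that the two could be compared.

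**Working it through.** **Step 1: compare the texts on one patient.** Take a patient who stops sessions at week 5 and answers the week-12 interview.
- General Statistical Approach: the patient stays in the assigned arm and stopping is irrelevant, so the week-12 score counts.
- Intercurrent-event paragraph: discontinuation is a listed event, so the scores at week 12, 6 months and 12 months are all left out.

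The primary questionnaires have no scheduled administration between baseline and week 12. This patient therefore brings only a baseline score to the mixed model and almost no information to the week-12 contrast. The premise that later outcomes can be predicted from earlier ones then rests on baseline and covariates alone. The paragraph makes no exception for a paused patient who resumes.

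**Step 2: can the excluded scores exist?** Stopping or pausing sessions does not by itself prevent a telephone interview at home. After clinic transfer, peritoneal dialysis or transplant the position is less clear, because the protocol counts these as loss to follow-up. The loss of usable scores is therefore chiefly after discontinuation and COVID pause.

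**Step 3: inputs for size.** The plan gives no figure for the gap between the two effects. Its design effect of 0.6 SD serves as the reference. The plan's power at that effect reproduces acceptably with 136 / 2 = 68 per arm: 93.5% against the stated 93% unadjusted, and 86.1% by simulation against 88% with false-discovery-rate control over three endpoints. Power is not used below.

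Assumed, because the protocol gives neither:
- q = share of the TACcare arm with an event before week 12
- r = share of the benefit retained afterwards

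**Step 4: formula.** With no post-event change in controls:

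treatment-policy effect = 0.60 × [1 − q × (1 − r)]

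| q | r = 0 | r = 0.5 | r = 1 |
|---|---|---|---|
| 10% | 0.60 × 0.90 = 0.54 | 0.60 × 0.95 = 0.57 | 0.60 |
| 20% | 0.60 × 0.80 = 0.48 | 0.60 × 0.90 = 0.54 | 0.60 |

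The hypothetical effect is larger by 0.60/0.54 − 1 = 11% to 0.60/0.48 − 1 = 25% at r = 0, by 5% to 11% at r = 0.5, and by nothing at r = 1.

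**Step 5: can the order reverse?** Suppose 14% of both arms have an event, TACcare patients keep the full 0.60, and controls worsen by 0.30 SD afterwards. The treatment-policy effect is 0.60 − 0.14 × (−0.30) = 0.642, above 0.60. Here 14% is only an assumed event rate; the protocol's 14% is attrition.

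**Step 6: check with the planned type of model.** A small random-intercept simulation used q = 14% in both arms and a true hypothetical effect of 0.60. It had few replicates, with Monte Carlo error of about 0.03 to 0.05.

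| Benefit retained | Post-event data kept | Post-event data deleted |
|---|---|---|
| none | 0.53 | 0.64 |
| half | 0.54 | 0.58 |
| all | 0.60 | 0.59 |

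Within that error, this agrees with the formula.

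**The case against.** The strongest reply is that the hypothetical target is open and reasoned. The paragraph names the strategy, the events, the quantity estimated and the assumption. The Summary of Major Revisions dates the estimand approach to September 2020, on the suggestion of a funder biostatistician, before unblinding on 25 August 2022. Which strategy is primary for each event is partly a design choice, and a hypothetical strategy is easier to defend for a COVID pause than for most events. All of this stands. A reader might infer a concealed estimand; the documents do not support that. The fault is a label left in place beside a rule that contradicts it.

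It may also be said that intention-to-treat only means keeping everyone in the assigned arm. That does not reconcile the texts, because the protocol's own definition goes further and rules out any role for adherence or withdrawal.

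The protocol plans sensitivity analyses for missing data and will consider pattern-mixture and selection models. These could probe the prediction assumption, but none restores the excluded scores. A separate statistical analysis plan might name an analysis that does; it would not remove the conflict within the protocol.

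Stronger readings are tempting but unsupported:
- **That the primary result is biased in favour of TACcare.** This needs lost benefit after the event and stable controls. Steps 4 and 5 show that the effects can be equal or reversed.
- **That stopping will differ by arm.** Patients are unblinded and coordinator sessions number 12 against 6, but controls have weekly contact, alternating with educational material, and no discontinuation rate is given for either arm.
- **That the rule undoes the increase to 160.** Any further data loss has no source and may overlap the 14% attrition.
- **That many scores after relocation or modality change are deleted.** The eligibility criteria exclude several such moves when planned within 6 months, and the loss-to-follow-up wording suggests that little may be collected afterwards.

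**Conclusion.** The contradiction holds on the text alone. The primary analysis as specified in the intercurrent-event paragraph lacks the property claimed for it in the Study Overview and the General Statistical Approach. The two descriptions target different effects unless benefit fully persists after the event or offsetting changes happen to cancel.

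The size cannot be fixed from the protocol. Under the stated assumptions (10% to 20% of the TACcare arm with an event before week 12, controls unchanged), the gap from 0.60 SD is 0.06 to 0.12 SD with no benefit retained and 0.03 to 0.06 SD with half retained. Only events before the week-12 interview alter the primary contrast in this way. The more favourable direction is plausible for the hypothetical analysis but not established.

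**What to change.** Reconcile the Study Overview, General Statistical Approach, Sensitivity analyses and Intercurrent events paragraphs on one primary estimand, by one of two routes:

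1. Use treatment policy for treatment discontinuation and pause, keeping all observed 12-week, 6-month and 12-month telephone scores, and report the hypothetical analysis as supplementary. This matches the intention-to-treat wording and the effectiveness aim.
2. Keep the hypothetical strategy as primary, stop calling it intention-to-treat, and pre-specify a treatment-policy analysis that uses all observed scores.

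Under either route, state separately how death is handled. Reconcile the loss-to-follow-up definition with the home telephone assessments, so that outcomes that can still be collected after clinic transfer or modality change are kept. Because the protocol records unblinding in August 2022, a change of primary strategy, or an analysis added, after that date should be dated and declared as post hoc.

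The cost is wording, one more model run and possibly a smaller estimated effect.

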## Summary of Major Revisions to the SAP

1. To gain efficiency, primary analyses adjusted for variables used in stratification as detailed in the design paper (October 2018). Prior to study results unblinding to the study team on August 25, 2022, sex was also added to the model.
2. Subgroup analyses based on charlson comorbidity were made consistent with the cutpoint used in the stratified randomization (CCI $<$ 4 and CCI $\geq$ 4) as detailed in the design paper (October 2018).

Subgroups based on elevated symptom at baseline were also examined to determine if the treatment effects could be different among those who have elevated symptoms at baseline. This was added prior to the study results unblinding to the study team on August 25, 2022.

3. Item-level imputation was performed prior to calculating scores to minimize missing data. This plan was added prior to study results unblinding to the study team on August 25, 2022.
4. To handle intercurrent events (ICE), the estimands approach from the ICH E9 R1 was adopted [Mallinckrodt CH, Bell J, Liu G, Ratitch B, O'Kelly M, Lipkovich I, Singh P, Xu L, Molenberghs G. Aligning Estimators With Estimands in Clinical Trials: Putting the ICH E9(R1) Guidelines Into Practice. *Ther Innov Regul Sci*. 2020 Mar;54(2):353-364. doi: 10.1007/s43441-019-00063-9. Epub 2020 Jan 6. PMID: 32072593]. This was suggested by an NIDDK biostatistician when the study size was requested to be increased. (September 2020)
5. Due to lack of access to Morisky medication adherence scale which will be used to define the per-protocol set, the per-protocol analyses were not performed.
6. A joint longitudinal model was also used as an alternative model for the three primary outcomes as recommended by the biostatistical reviewer. (March 2023)

| Patient-Reported Outcome (PRO) instruments (Appendix)                                                    |              |                                                             |                                                                                                                                                                                                                                                                                   |
|-----------------------------------------------------------------------------------------------------------------|--------------|-------------------------------------------------------------|-----------------------------------------------------------------------------------------------------------------------------------------------------------------------------------------------------------------------------------------------------------------------------------|
| Questionnaire                                                                                            | Items | Domains                                              | Psychometric properties                                                                                                                                                                                                                                                    |
| Beck Depression Inventory-II (BDI-II)                                                                    | 21           | Depression                                                  | Excellent internal consistency, test-retest validity and high sensitivity, specificity and responsiveness to treatment in HD population                                                                                                                          |
| Functional Assessment of Chronic Illness Therapy Fatigue (FACIT-F)                                       | 13           | Fatigue                                                     | Excellent internal consistency, test-retest reliability, responsiveness to interventions and good correlation with SF-36 measured fatigue in HD patients                                                                                                        |
| Brief Pain Inventory (BPI) Short form                                                                    | 9            | Pain                                                        | Extensively used in HD, Excellent construct validity, reliability and responsiveness to treatment                                                                                                                                                                   |
| Pittsburgh Sleep Quality Index (PSQI)                                                                    | 19           | Sleep quality                                               | Good internal homogeneity, test-retest reliability, discriminant validity, is responsiveness to treatments and has been used in the ESRD population                                                                                                             |
| Medical Outcomes Study Short Form-12 (SF-12)                                                             | 12           | Health-related quality of life                              | The SF-12 scores have excellent intra-class correlation of 0.94 with the SF-36.  SF-36 is commonly used in HD patients, and has been extensively tested for reliability and validity in HD patients, well-accepted, responsive to clinical change  |
| Multi-dimensional Scale of Perceived Social Support                                                      | 12           | Perceived social support                                    | Has 3 subscales—family, friends, and significant others, has good internal and test-retest reliability and has been used in ESRD patients                                                                                                                       |
| Generalized Anxiety Disorder-7 (GAD-7) scale                                                             | 7            | Anxiety                                                     | Excellent internal consistency, reliability and validity in the general population                                                                                                                                                                                  |
| NIH Patient Reported Outcomes Measurement Information System (PROMIS) Adult Global Health questionnaire. | 29           | Physical function, fatigue, pain, emotional distress, sleep | These domains have excellent internal consistency, convergent validity and significant differences between health and disease                                                                                                                                       |
| Physical Activity Scale for Elderly (PASE)                                                               | 10           | Physical activity                                           | Measures physical activity over last 7 days and has been shown to correlate with accelerometry data in HD patients                                                                                                                                                  |

